## Abstract

This pilot multicentered, randomized, parallel, sham-controlled trial is intended to evaluate the effectiveness and safety of electroacupuncture therapy for poststroke patients with urinary incontinence. Forty stroke survivors aged >19 years will be recruited in 2 hospitals in the Republic of Korea. Patients who experienced stroke within 2 years and satisfy criteria of urinary frequencies ≥2 with either 3 to 4 points on the Patient Perception of Intensity of Urgency Scale or 13 points or more on the Korean version of the International Prostate Symptom Scale (K-IPSS) will be identified, along with other eligibility criteria. Patients will be randomly allocated to either a treatment or control group to receive 10 sessions of electroacupuncture or sham therapies, respectively. Patients and outcome assessors will be blinded. The primary outcome is the change of Total Urgency and Frequency Score between the baseline and the trial endpoint. The K-IPSS, the International Consultation on Incontinence Questionnaire for Urinary Incontinence Short Form, and the Lower Urinary Tract Symptoms Outcome Score will be evaluated for effectiveness assessment. Adverse events will be reported after every session. The Blinding Index will also be calculated. Data will be statistically analyzed with 0.05 significance levels by 2-sided testing.

## 1. Background

Urinary incontinence (UI) is defined as involuntary loss of urine [1], with reduced ability either to be aware of bladder signals before leakage or to take notice of eventual leakage or both [2]. The damaged neurological lesions in the brain of stroke survivors lead to loss of control of detrusor function, which is the reason that poststroke patients often experience UI [3, 4].

A previous study reviewed 9 papers from European countries, USA, and Japan and reported that the UI prevalence in stroke patients was estimated by 32% to 79% at admission and 25% to 28% at discharge [4]. A study suggested that the prevalence of poststroke urinary incontinence (PSUI) might be as high as 45.6% in Korea, which is higher than that of UI [5].

Urinary dysfunction generally affects the quality of life in stroke survivors [6], but the development of UI following a stroke is also a predictor of future functional recovery after acute stroke [7], with a strong association with both increased mortality rates and poor functional outcomes [8]. As a result, clinicians and researchers have been highly interested in the management or treatment of poststroke UI.

Recommended treatments for poststroke UI include bladder retraining, timed or prompted voiding, intermittent catheterization, the use of anticholinergic medications, and environmental and lifestyle support, none of which have sufficient evidence of efficacy, according to a systematic review [8]. Acupuncture therapies have been also explored for the management of UI after stroke in China. For example, stroke survivors who received acupuncture showed lower rates of UI than those who received no treatment or usual care, even though the quality of studies was questionable [8]. Another review implied that acupuncture or acupressure therapies exhibited favorable effects on UI patients with overactive bladder symptoms and suggested that a more qualified randomized controlled trial (RCT) should be implemented [10]. A Chinese study conducted a multicenter RCT and reported the positive clinical efficacy of electroacupuncture (EA) for apoplectic UI compared with indwelling catheterization [11].

However, there have been no RCTs to determine whether EA is effective for UI in poststroke patients compared with a sham comparator. This pilot study is aimed at evaluating the effectiveness and safety of EA therapy for poststroke patients with UI, to explore suitable conditions for a future full-scale RCT.

## 2. Methods

### 2.1. Study Overview 

#### 2.1.1. Design and Setting

This is a pilot multicentered, randomized, parallel, sham-controlled trial. Two hospitals in Korea (Kyunghee University Korean Medicine Hospital in Seoul and Wonkwang University Gwangju Medical Center in Gwangju) will recruit the participants. The Consolidated Standards of Reporting Trials (CONSORT) [12], Standards for Reporting Interventions in Clinical Trials of Acupuncture (STRICTA) [13], and Standard Protocol Items: Recommendations for Interventional Trials (SPIRIT) 2013 [9] guidelines were followed for development of this trial protocol. A schematic diagram to summarize the schedule of enrollment, interventions, assessments, and visits for participants, recommended by SPIRIT 2013, is depicted in Table 1.

#### 2.1.2. Ethical Committee Approval

The institutional review board in Kyung Hee University Korean Medicine Hospital approved this trial (KOMCIRB-160215-HR-006). The protocol was registered at ClinicalTrials.gov on Jun 29, 2016 (identifier no. NCT02819336).

### 2.2. Study Participants

#### 2.2.1. Inclusion Criteria

Forty patients diagnosed with PSUI will be recruited, satisfying all the following inclusion criteria: (a) male or female aged over 19 years; (b) survivor of stroke due to cerebral hemorrhage or infarction diagnosed by computed tomography or magnetic resonance imaging within 2 years; (c) patient with 2 or more urinary frequencies with 3 to 4 points on the Patient Perception of Intensity of Urgency Scale (PPIUS) or who scored 13 points or more on the Korean version of the International Prostate Symptom Scale (K-IPSS); and (d) any volunteer who signed an informed consent form.

#### 2.2.2. Exclusion Criteria

We will screen out patients who meet any of the following exclusion criteria: (a) 1 or more postvoiding residual volumes >200 mL per day; (b) clinically significant stress UI diagnosed on cough induction test or investigator's clinical experience; (c) recurrent urinary tract infection (UTI), defined as 4 or more UTIs requiring treatment in the prior 1 year; (d) cognitive impairment with 23 points or less on the Korean version of the Mini-Mental State Examination; (e) acute or chronic lower UTI examined by urine culture; (f) preexisting UI before the stroke occurred, with UI symptoms since then; (g) any major diseases in the lower urinary tract; (h) coagulation disorders; (i) medical or surgical procedures for peripheral arterial diseases; (j) psychiatric diseases; (k) fear of acupuncture; (l) pregnancy (examined by urine test); or (m) any other appropriate reason based on the clinical experience of the primary or subinvestigator. The investigators will take and record the medical history to determine the existence of criteria (f), (g), (h), (i), and (j).

Screening assessment will be conducted after we obtain informed consent forms from all voluntary candidates. For patients aged 75 years or older, we will offer more easily understood literature and consent forms. A copy of the signed consent will be given to the participants.

#### 2.2.3. Dropout Criteria

Participants will be dropped out when any one of the following criteria apply: (a) any of the aforementioned exclusion criteria is found after the patient screens in; (b) patients or their legal representatives withdraw consent or want to suspend participation; (c) investigators lose contact with the participant; (d) investigators or patients violate the trial protocol; (e) patients have serious or permanent injury from the trial; (f) patients take any drugs that can affect the results of the trial without direction by the investigators during the trial; or (g) patients have other sufficient reasons to interrupt the trial progress, as determined by investigators' clinical experience.

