#### 2.2.4. Sample Size Calculation

Because there is no preceding study to evaluate the effectiveness of EA for PSUI using the Total Urgency and Frequency Score (TUFS), with a control of any sham devices, we reviewed a statistical study on the appropriate group size for a pilot study. One study suggested that at least 12 participants should be recruited in each group to conduct a pilot trial [14], and another suggested that an increase in size from 12 to 18 or 24 narrowed the confidence interval [15]. Accordingly, we decided that 18 participants per group would be adequate. Therefore, with anticipated dropout rates of 10%, totally 40 participants (20 per group) will be randomized and allocated each EA or sham acupuncture (SA) group.

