### 2.3. Randomization and Group Allocation

An independent statistician will generate a singular sequence of random numbers using the R program (R Foundation for Statistical Computing, Vienna, Austria. http://www.r-project.org/) for the entire study. The participants will be given a unique screening number by the order of signing of informed consent, and they will be randomly allocated to either the EA or SA group.

After requesting group allocation, the investigators will receive an email or text message from the statistician including the group assignments for the patients. The allocation ratio is 1 : 1 (20 in the EA group or SA group, resp.).

The electronic file with random sequence and allocation information can be accessed by the independent statistician until the trial cessation or closeout.

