#### 2.5.3. Concomitant Medications

According to clinical practice guidelines [19], conventional treatments for stroke and complex management with drugs (antiplatelet agents, anticoagulants, or neuroprotectants), rehabilitation therapies, traditional herbal medications, EA (except for the CV2, CV3, CV4, CV6, SP6, and SP11 acupoints), acupuncture, and moxibustion will be allowed during the study for both groups. In addition, conventional treatments for UI such as oral medications, including diuretics, bladder rehabilitation training, traditional herbal medications, EA (except for the CV2, CV3, CV4, CV6, SP6, and SP11 acupoints), acupuncture, and moxibustion are permitted. However, treatment strategies of fluid therapy and oral administration of any UI drugs should not be changed from 3 days before the trial to the end, because they can significantly affect the symptoms of UI.

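### The dropout rule orders removal for events after which the patient can usually still be assessed, and does not separate stopping sessions from leaving the study

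*Protocol article*

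**What the plan says.** Protocol article, section 2.2.3 (Dropout Criteria), opens with a mandatory rule: "Participants will be dropped out when any one of the following criteria apply". Seven criteria, (a) to (g), follow under one status.

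- Two inherently tend to end data collection: (b) withdrawal of consent, which is pooled with a wish to suspend participation, and (c) lost contact.
- Four usually leave the patient assessable: (a) "any of the aforementioned exclusion criteria is found after the patient screens in"; (d) "investigators or patients violate the trial protocol"; (f) "patients take any drugs that can affect the results of the trial without direction by the investigators during the trial"; and (g) "patients have other sufficient reasons to interrupt the trial progress", as judged by investigators.
- Criterion (e), serious or permanent injury from the trial, often leaves the patient assessable too.

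Related provisions elsewhere in the article:

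- Section 2.2.4 sizes the trial "with anticipated dropout rates of 10" percent.
- Section 2.3: "the investigators will receive an email or text message from the statistician including the group assignments for the patients". Section 2.4 blinds patients and outcome assessors only.
- Section 2.5.3: "oral administration of any UI drugs should not be changed from 3 days before the trial to the end".
- Section 2.6.1 and Table 1 schedule the outcome TUFS twice, at V2 (baseline) and V13 (closeout). Table 1 has no early-termination visit.
- Section 2.7 defines the FAS by at least 7 sessions and at least one TUFS, the PP set by all 10 sessions, and imputes missing values by LOCF.

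**The concern.** The rule does not distinguish a patient who stops needling from one who leaves the study. Criterion (d) has no threshold and covers the investigator's own violations. Nothing in the article says that a dropped patient is still assessed at V13. If the rule is followed as written, endpoint scores that could have been obtained are likely to be lost because of the rule itself.

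Such losses need not be random. A patient who changes a UI drug unprompted, perhaps because symptoms worsened, breaches section 2.5.3 and so meets (d), and also (f) if the change is a newly taken drug. Criterion (g) rests on the judgement of investigators who are sent the allocation, so it can be applied with the arm known. Section 2.2.3 names no decision-maker for (d) or (f).

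At stake are the TUFS comparison and the estimates that the Discussion says will be used to size a full-scale trial.

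**Working it through.** **1. The plan's own figure.** 18 per group with 10% dropout gives 18 / (1 − 0.10) = 20 per group, 40 in total. This matches section 2.2.4. The point does not rest on a sample size error. The allowance corresponds to 0.10 × 20 = 2 dropouts per arm, for all reasons.

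**2. What happens to a dropped patient's TUFS if V13 is not collected.**

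- At least 7 sessions: the baseline TUFS satisfies the FAS requirement of one primary outcome. It is also the only observation, so LOCF carries it forward and the change is 0.
- Fewer than 7 sessions: the patient is outside the FAS. That follows from section 2.7, so no figure is attributed to the dropout rule for these patients.

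**3. Size for late removals.** All inputs except the 20 per arm are assumptions.

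- k = patients removed in one arm after at least 7 sessions, with none in the other
- m = the arm's mean TUFS change in SD units, from 0 to −0.5 (negative is improvement)
- d = how much worse the removed patients would have scored than their arm mean, in SD

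LOCF replaces each change of m + d by 0, so the arm mean shifts by −k(m + d)/20.

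| d | k | m = 0 | m = −0.5 |
|---|---|---|---|
| 1.5 | 2 | −2(1.5)/20 = −0.15 | −2(1.0)/20 = −0.10 |
| 1.5 | 3 | −3(1.5)/20 = −0.225 | −3(1.0)/20 = −0.15 |
| 0.5 | 2 | −2(0.5)/20 = −0.05 | 0 |
| 0.5 | 3 | −3(0.5)/20 = −0.075 | 0 |

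Imputed patients stay in the analysis, so with an SD of 1 the standard error of the difference is √(2/20) = 0.316 SD. The largest shift is 0.225 / 0.316 = 0.71 standard errors.

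**4. Direction.** Setting worsened sham patients to zero flatters sham and works against EA. Setting worsened EA patients to zero works for EA.

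**5. Balanced removals.** Take 2 per arm, EA m = −0.5, sham m = 0, and the same d in both arms.

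- EA: −0.5 − 2(−0.5 + d)/20 = −0.45 − 0.1d
- Sham: −2d/20 = −0.1d
- Difference: −0.45 for any d, so a true 0.5 SD effect shrinks by 0.05 SD

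**6. Limit of the formula.** Here m + d stands for the score that would have been observed at V13. For a patient who changed a UI drug, that score would reflect the new drug, not the untreated worsening, so large values of d may not apply to that trigger.

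**The case against.** The strongest reply is that the harm is inferred. A reader might take section 2.2.3 to say that V13 is cancelled or collected data discarded; it says neither. The article condenses a full protocol that is not shown, and follow-up after discontinuation is the kind of detail an article may leave out. The missing early-termination visit in Table 1 therefore proves little. This stands as a limit on the consequence. It does not remove the rule that is printed: mandatory removal, one status for all triggers, and no assessment described afterwards.

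Second, the FAS keeps patients with 7 to 9 sessions, so (d) may not be meant literally. That is fair. A reader might argue the reverse from the PP definition, which has no exclusion for violations, and infer that violators must already have been removed. That is speculation; a condensed definition explains it equally well. What remains is that a site cannot tell from 2.2.3 which deviations require removal.

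Third, part of the mechanism belongs to other rules. The zero change comes from LOCF with two TUFS time points, the loss of patients below 7 sessions from the FAS definition, and knowledge of the arm from section 2.3. This is correct. The dropout rule's own share is that it can create missing scores where none need exist.

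Fourth, the largest case is demanding: three late removals in one arm, none in the other, each 1.5 SD worse than the arm mean. Three exceeds the 2 per arm that the plan allows for all dropout, and the window is only the end of an 18-day course. The milder inputs give 0 to 0.08 SD. This also stands.

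Finally, some triggers justify stopping needling, such as pregnancy or a coagulation disorder found late under (a), and (f) leaves out drugs taken at the investigators' direction. Stopping treatment is still not a reason to omit a diary and questionnaires.

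**Conclusion.** The point holds as a defect in a stated rule. Section 2.2.3 requires dropout for (a), (d), (f), (g) and often (e) where the patient can usually still be assessed, and it does not separate treatment stop from study exit. Loss of the V13 TUFS is the natural reading, not an explicit statement.

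The EA-sham difference and the estimates meant for the full trial can be biased in either direction. The actual size cannot be found from the article. Under the assumed inputs for removals after at least 7 sessions, it ranges from 0 to about 0.2 SD, at most about 0.7 standard errors.

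A reader might infer that the trial's result will be biased in a known direction, or by the upper figure. The documents support neither: the number, timing, arm and outcomes of removed patients are all assumed. This is a cheap improvement that should be made, held with moderate confidence.

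**What to change.** In section 2.2.3, define two statuses.

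- **Leaves the study:** only on withdrawal of consent for further data, or loss of contact.
- **Stops study treatment:** for the other criteria, stop sessions where needed (for example injury, pregnancy or coagulation disorder), but still collect the V13 assessments already in Table 1 (PPIUS/TUFS, ICIQ-UI-SF, K-IPSS, LOS and the blinding question) at the scheduled time.

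Use the observed V13 score in place of LOCF, and report treatment stops and study exits separately by reason and arm. For patients with fewer than 7 sessions this helps only if the FAS in section 2.7 is also changed to include randomised patients with a V13 TUFS whatever their session count. If the full protocol already provides for V13 after stopping, say so in 2.2.3.

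The cost is protocol wording plus one closing diary and questionnaire set for each patient who stops early. The downside is that some V13 scores will reflect incomplete treatment or changed drugs. The comparison then estimates a treatment-policy effect, which may dilute the EA-sham difference if EA works.

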#### 2.2.4. Sample Size Calculation

Because there is no preceding study to evaluate the effectiveness of EA for PSUI using the Total Urgency and Frequency Score (TUFS), with a control of any sham devices, we reviewed a statistical study on the appropriate group size for a pilot study. One study suggested that at least 12 participants should be recruited in each group to conduct a pilot trial [14], and another suggested that an increase in size from 12 to 18 or 24 narrowed the confidence interval [15]. Accordingly, we decided that 18 participants per group would be adequate. Therefore, with anticipated dropout rates of 10%, totally 40 participants (20 per group) will be randomized and allocated each EA or sham acupuncture (SA) group.

### 2.3. Randomization and Group Allocation

An independent statistician will generate a singular sequence of random numbers using the R program (R Foundation for Statistical Computing, Vienna, Austria. http://www.r-project.org/) for the entire study. The participants will be given a unique screening number by the order of signing of informed consent, and they will be randomly allocated to either the EA or SA group.

After requesting group allocation, the investigators will receive an email or text message from the statistician including the group assignments for the patients. The allocation ratio is 1 : 1 (20 in the EA group or SA group, resp.).

The electronic file with random sequence and allocation information can be accessed by the independent statistician until the trial cessation or closeout.

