### 2.7. Statistical Analysis

Categorical variables will be presented with frequencies and percentage and analyzed by *χ*
^2^ test or Fisher's exact test for demographic information and adverse events. Continuous variables will be presented with mean ± standard deviation and analyzed by two-sample *t*-test or Mann-Whitney *U*-test for demographic information and effectiveness outcomes, depending on the normality of the baseline distribution. If necessary, efficacy data will be evaluated with analysis of covariance (ANCOVA) with covariates of recruiting center and any demographic information, such as gender.

Full analysis set (FAS) (defined as the data set of the participants who receive 7 or more EA or SA sessions and provide the primary outcome at least once) will be primarily used for the effectiveness assessment. Per-protocol (PP) analysis (defined as the data set of the participants who complete every 10 EA or SA session) will be subordinately adopted. Missing data will be imputed by the last observation carried forward method. For the safety assessment, safety set analysis will be performed with the data obtained from all of the participants who receive at least one EA or SA session.

Finally, for the BI assessment, the distribution of actual allocation and participant's responses (EA group, SA group, or DO NOT KNOW) will be presented with 2 × 3 cross tabulation along with the index calculation.

IBM SPSS Statistics for Windows (Version 21.0. IBM Corp. Released 2012. Armonk, NY, USA) will be used, with 0.05 significance levels by a 2-sided test.

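### One random sequence serves both hospitals and centre adjustment is optional, so neither the design nor the default analysis protects against chance imbalance by centre

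*Protocol article*

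**What the plan says.** Section 2.1.1 of the protocol article has "Two hospitals in Korea" recruiting. Section 2.3 states that the independent statistician "will generate a singular sequence of random numbers using the R program", and that this one sequence is "for the entire study". The statistician sends each assignment to the investigators by email or text on request. The ratio is 1:1, with "20 in the EA group or SA group".

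Section 2.7 compares the effectiveness outcomes with a two-sample t-test or a Mann-Whitney test, chosen on baseline normality. An ANCOVA with "covariates of recruiting center" and demographic variables is added only if needed, and no rule says when it is needed.

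Section 2.2.4 explains the size: "we decided that 18 participants per group would be adequate", raised to 20 per group for 10% dropout. The expected number of patients per hospital is not given.

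**The concern.** A single sequence across two sites is a stated choice, so the lack of stratification by hospital is not merely a detail that a condensed article left out. The plan itself puts centre first among its possible covariates.

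There are reasons to expect hospitals to differ. Section 2.5.3 permits a wide range of concomitant stroke and incontinence care. Some exclusions in section 2.2.2 rest on the investigator's judgement. Different practitioners will presumably treat at each site. That these features do differ between the two hospitals is an inference; the document gives no data by centre.

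If centre is related to outcome and the arms are unevenly spread over the hospitals, part of any centre difference appears as a treatment difference in the unadjusted comparison. Section 3 intends to use the results to size a full-scale trial, so an observed effect displaced by a centre imbalance could carry into that calculation. Leaving adjustment to a later, unspecified decision also means that the choice may be made after the imbalance and the result are known.

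**Working it through.** **The plan's own figure.** 18 evaluable per group with 10% dropout: 18 / 0.9 = 20 per group, so 2 × 20 = 40. This reproduces section 2.2.4.

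**Inputs.** Total 40, with 20 per arm (sections 2.2.4 and 2.3); two hospitals (section 2.1.1). Patients per hospital: not stated, assumed 20 each, with smaller values tried below. The list is taken in the way most favourable to the plan, as exactly 20 EA and 20 SA places in random order.

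**Split within a hospital.** If m patients come from one hospital, the number X on EA is hypergeometric: P(X = k) = C(20, k) × C(20, m − k) / C(40, m).

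For m = 20:

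- exactly 10:10: 24.8%
- 12:8 or worse, in either direction: 34.3%
- 13:7 or worse: 11.3%

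For a smaller second hospital:

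- m = 15: 10:5 or worse, 19.1%
- m = 10: 7:3 or worse, 27.3%
- m = 8: 6:2 or worse, 23.5%

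**Effect on the unadjusted difference.** Let the hospitals differ by d within-centre SD. With X of the 20 EA patients and (m − X) of the 20 SA patients from the first hospital, the shift is [X − (m − X)] / 20 × d.

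- 13:7 against 7:13: (13 − 7) / 20 = 0.30d
- 12:8 against 8:12: (12 − 8) / 20 = 0.20d
- 7:3 (m = 10) or 6:2 (m = 8) in the smaller hospital: 4 / 20 = 0.20d

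For an assumed d of 0.5, these are 0.15 SD for the first and 0.10 SD for the others. For d = 1.0 they are 0.30 and 0.20 SD.

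**Comparison with sampling error.** The standard error of the difference at 20 per arm is √(1/20 + 1/20) = 0.316 SD. A shift of 0.15 SD is about half of that (0.15 / 0.316 = 0.47).

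**Average loss of precision.** With equal hospitals and no adjustment, centre adds d²/4 to the patient variance. For d = 0.5 the standard error becomes √[(2/20) × (1 + 0.0625)] = 0.326, about 3% more than 0.316. The average cost is small; the concern is the less likely but larger shift in the one trial that is run.

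**What adjustment alone achieves.** With centre in the model, the shift is removed even at 13:7 and 7:13. The price is a relative efficiency of 4 × 13 × 7 / 400 = 0.91, or 0.96 at 12:8. Stratified allocation largely avoids that price as well.

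**The case against.** The strongest reply is that randomisation needs no stratification to be valid. Imbalance by centre does not bias the comparison in expectation, and its contribution is already in the unadjusted standard error, as the 0.326 above shows. With a centre difference of 0.2 to 0.5 SD, a 12:8 split moves the estimate by only 0.04 to 0.10 SD. In a two-centre pilot of 40, stratification can fairly be called a preference, and a fixed centre term would deal with most of the problem. All of this stands, and it limits the point to a cheap improvement.

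A reader might infer more from section 2.3 than it supports:

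- **That the sequence is unrestricted and will not deliver 20:20.** The section does not describe the restriction, but it does state 20 in each group. Ranking 40 random numbers and giving 20 places to each arm is a single random sequence that produces exactly that. Block details are also what an article may leave to the full protocol. Nor does the text say that list positions follow the screening numbers given at consent, in which case screening failures would use up places.
- **That the planned 18 per group would be missed.** This depends on the same unsupported reading.
- **That estimates by centre would become unusable.** The plan announces no such estimates, and within-hospital efficiency would still be 0.91 at 13:7.

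**Conclusion.** The point holds in a limited form. Allocation is not stratified by hospital, and the default analysis ignores hospital, so centre is secured at neither stage. With the list fixed at 20:20 and an assumed 20 patients per hospital, the chance is about one in three (34%) of 12:8 or worse within a hospital, and about one in nine (11%) of 13:7 or worse. The latter displaces the unadjusted effect by 0.15 SD if the hospitals differ by 0.5 SD, roughly half a standard error.

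The probabilities rest on the assumed recruitment per hospital, and the displacement on the assumed centre difference; the document supplies neither. The consequence is chance confounding and modest lost precision, not systematic bias. The point does not show that the stated 20:20 fails.

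**What to change.** Two changes to stated rules:

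1. **Section 2.3.** The same independent statistician generates one list per hospital in randomly permuted blocks of varying size, with the sizes withheld from the sites. Assignments go out by the existing email or text route.
2. **Section 2.7.** Make the ANCOVA with centre the fixed primary analysis, in place of adjustment only if necessary. If a rank test is kept for non-normal data, stratify it by centre.

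One sentence stating how 20 per arm is obtained would also remove the misreading described above.

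The cost is a few lines of R before the first allocation and two sentences of text; the total stays at 40. There are two drawbacks. The ends of blocks become slightly more predictable, which varying, concealed sizes and central release keep small. Unfinished blocks can also leave the overall split off 20:20: with blocks of 4 and 6 the difference is at most 3 in each hospital, so at most 6 overall, or 23:17. If allocation has already begun, the second change can still be made before unblinding and covers most of the concern.
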